## 2.2 Recombinant Vaccinia Virus Vaccine

### 2.2.1 Research of replication competent viral vector vaccines

Currently, MVA (Modified Vaccinia Virus Ankara), ALVAC (Avipoxvirus Canarypox), and NYVAC (Copenhagen Strain of Vaccinia Virus) are the most extensively studied and widely used poxvirus vectors. Clinical trials have shown that these non-replicating vaccinia virus vector vaccines are very safe in humans, but their immunogenicity is relatively weak, and the immune responses they induce in humans are significantly weaker than those in monkeys [12, 26]. Although the reasons for the significant differences in immune effects between humans and animals are not yet clear, the weak immunogenicity of these vaccines may be related to the non-replicative nature of the vectors. After infecting host cells, these vector vaccines can only undergo one cycle of antigen expression, processing, and presentation, and cannot produce infectious viruses. Their stimulation of the immune system is limited and transient. In contrast, replicating vaccinia virus vectors can persistently and repeatedly stimulate the immune system over a longer period, thereby inducing strong immune responses in the body, which holds promise for long-term immune protection and memory.

Replicating recombinant poxviruses can protect animals against many veterinary diseases. Currently, several recombinant poxvirus veterinary vaccines have been approved for use. Replicating recombinant poxviruses as vectors for hepatitis B virus, Epstein-Barr virus, and therapeutic cancer vaccines have entered the human immunization observation phase, with some showing good immune effects [27-29]. In the SIV-macaque model, initial immunization with a recombinant vaccinia virus expressing the SIV env gene, followed by a boost with Env

protein, protected macaques from challenge with homologous strains [30]. The phase I clinical trial of a replicating recombinant vaccinia virus (HIVAC-1e) expressing HIV-1 env, developed by Cooney EL et al., showed that a booster immunization eight weeks after the initial HIVAC-1e vaccination could induce HIV-1-specific T lymphocyte proliferative responses and Env-specific antibodies lasting more than a year in test subjects who had not previously received the smallpox vaccine [31]. These results suggest that HIV vaccines based on replicating poxvirus vectors may have promising applications.

Since its isolation in the 1920s, the vaccinia virus Tian Tan strain has been used for smallpox prevention for several decades, immunizing over a billion Chinese people. Vaccinia virus is generally harmless to humans, causing only local, short-term symptoms at the vaccination site, with a very low incidence of more serious adverse reactions. The incidence of post-vaccination encephalitis with the Tian Tan strain is 0.5 per million, progressive vaccinia is 0 per million, and post-vaccination eczema and generalized vaccinia are 1 per million, making it safer than smallpox vaccine strains used in other countries. The high safety profile of the Tian Tan strain ensures its suitability as a vector for other vaccines.

### 2.2.2 Recombinant vaccinia virus vaccine

The vaccinia virus vector vaccine of this study is called recombinant vaccinia virus (rTV) AIDS vaccine, with the vector using Tiantan vaccinia strain 752-1, and is provided by Beijing Institute of Biological Products Co., Ltd. This Tiantan strain of vaccinia virus has been used in smallpox vaccine and extensively vaccinated in China.

The rTV vaccine expressed HIV genes are the main popular B'/C recombinant strain CN54 from China. The env (gp140TM), gag and pol genes act as the target genes and are inserted into TK region of vector. These HIV genes have been transformed to ensure the safety and immunogenicity of the vaccines.

We have manufactured 50,000 doses of rTV vaccines in compliance with GMP conditions, and all items are tested qualified and the test results are shown in Annex 5. Main information of rTV vaccine is shown in Table 2.

**Table 2. Main information of rTV vaccine**

| Vaccine     | Recombinant vaccinia virus (rTV)         |
|--------------------|-------------------------------------------------|
| Vector      | Vaccinia virus Tiantan 752—1                    |
| HIV-1 genes | gag, pol, and env                               |
| Titer       | 1.6×10  PFU/ml                      |
| Solvent     | 60% glycerol, 1 % to 2 % starch, 5.0 % albumose |

## 2.3 Summary of preclinical experiment

### 2.3.1 Safety evaluation in animal

The animal safety evaluation of the HIV-1 DNA vaccine and the rTV AIDS vaccine was

entrusted to the National Center for Safety Evaluation of Drugs at the National Institutes for Food and Drug Control, China. The test results demonstrated that both the DNA vaccine and the rTV vaccine exhibited good safety profiles in small animals.

### **2.3.2 Immunogenicity study in animal**

Immunization experiments have shown that three doses of the DNA vaccine can induce strong antigen-specific humoral and cellular immune responses in mice; however, a fourth dose of the DNA vaccine did not significantly enhance the immune response compared to three doses. Initial immunization with three doses of the DNA vaccine followed by a single booster with the recombinant vaccinia virus (rTV) significantly enhanced antigen-specific humoral immune responses, although the cellular immune responses varied depending on the antigen, with some increasing and others decreasing. Overall, the strategy of priming with the DNA vaccine and boosting with the rTV demonstrated advantages over DNA vaccine immunization alone.

Mouse immunization experiments with rTV indicated that the intramuscular route tended to induce humoral immune responses, while the intradermal route appeared to be more effective for inducing cellular immune responses, consistent with the skin scarification route used for smallpox vaccination. The strength of the immune response induced by rTV was positively correlated with the immunization dose, with both cellular and humoral immune responses increasing as the dose was raised.

Rhesus macaque immunization experiments demonstrated that the DNA vaccine induced strong antigen-specific humoral and cellular immune responses, which were significantly enhanced following a booster immunization with rTV.

SHIV challenge experiments in rhesus macaques revealed that three doses of rTV immunization provided protection against SHIV infection in all monkeys (4/4). Following a DNA prime-rTV boost regimen, one out of four test monkeys was protected against SHIV infection, two out of four showed viral load at 14 days post-challenge, but the peak viral loads were 2 log units lower than the average of the control group, and one monkey died from acute intestinal infection one week before the challenge, precluding results. In contrast, three out of four control monkeys that received empty vector inoculations had detectable viral replication by day 14 post-challenge. These results suggest that vaccination with the rTV AIDS vaccine can protect animals from SHIV infection.

Detailed information on the vaccine's safety, immunogenicity, and monkey challenge experiments can be found in the investigator's brochure.

## **2.4 Product Package, Doses and Method of Vaccination**

DNA vaccine is a colorless transparent liquid. It is supplied in 2ml vials with each vial of 2.0mg/1ml. The package specifies HIV-1 DNA vaccine (pGPNEF) or HIV-1 DNA vaccine (pGP140) and is stored at -70 °C. Each of the two plasmids was collected by 1ml for

intramuscular injection at the bilateral deltoids of upper arms.

The rTV vaccine is a pale yellow or light brown turbid and viscous liquid. It is supplied in 0.4ml/vial. The package indicates recombinant vaccinia virus (rTV) AIDS vaccine and is stored at -20 °C. The vaccination is performed with skin pricking method using a bifurcated needle. The vaccination method is as follows: insert the bifurcated needle into the vaccine vial, making it stained with enough vaccine liquid. Position your wrist against the vaccinated upper arm, perpendicularly direct the bifurcated needle to an area of 5mm in diameter at the deltoid of upper arm, and quickly prick 15 times. Prick with strength to the extent that bleeding points should appear at the pricking site in 15 to 30 seconds. If second smallpox will be vaccinated in the ipsilateral arm, another needle is needed to stain with vaccine for another vaccination at a site 2 cm away from the first vaccination site. When the site of vaccination becomes a little dry, it will be covered with gauze and dry breathable film.

Notes: Skin scarification is a conventional method of smallpox vaccination in China, and its operation process is as follows: first, drop 10μl vaccine (estimated dose of  $2 \times 10^5$  PFU) at the vaccination site and then scarifies to make the vaccine go through the damaged skin into body, but the actual amount of vaccine into body is much lower than 10μl. According to the international trend in this field, we use the immunization method with a bifurcated needle recommended by WHO in this clinical study. This method is simple in immunization procedure and easy to grasp as compared with the traditional ones. Using a bifurcated needle, dip for a volume of about 2.5μl, it has the same vaccination effect as a skin scarification vaccination using four times of dose (10μl). It ensures the effect of immunization while reducing the dosage of vaccine and improving the absorption rate of vaccine as compared to the traditional methods [32]. Each bifurcated needle dips this vaccine containing approximately  $0.4 \times 10^5$  PFU of rTV, and its immunization effect is equivalent to that of an estimated dose of  $1.6 \times 10^5$  PFU in a traditional skin scarification method.

The concentration of this rTV vaccine is  $1.6 \times 10^7$  PFU/ml, lower than the concentration of  $1.0 \times 10^8$  PFU/ml for smallpox vaccine recommended by WHO. In a recent study, however, the smallpox vaccine was diluted by 5 folds and 10 folds to the concentrations of approximately  $0.5 \times 10^8$ PFU/ml and  $1.0 \times 10^7$ PFU/ml, and was vaccinated using a bifurcated needle in volunteers. The results showed that the success rate was 98% to 100% for three concentrations of vaccines, and that there were no significant differences in the size of timing of skin lesions after vaccination of the three vaccines [33,34]. These results suggest that the concentration of this vaccine may not affect its vaccination effect.

### 3 Objectives and Rationale of the Study

The objective of this clinical trial is to evaluate the safety and immunogenicity of an AIDS DNA vaccine and a recombinant vaccinia virus vector vaccine in healthy volunteers. For this study, we have selected the B/C recombinant strain CN54 (CRF07), a prevalent HIV strain in China, as the pathogen model for designing the AIDS vaccine, providing a solid foundation for future vaccine evaluation and application. Existing research data indicate that DNA vaccines can induce protective immune responses specific to HIV and SIV in mice and primates, and there have been no reports of severe adverse reactions in humans following vaccination with such vaccines. Candidate AIDS vaccines based on vaccinia virus vectors have undergone several clinical trials, demonstrating good safety profiles and the ability to induce certain HIV-specific immune responses. The safety of the replicating vaccinia virus Tian Tan strain vector we employ has been validated through large-scale human application. Preclinical trial results have shown that the DNA vaccine and recombinant vaccinia virus vaccine we developed are well-tolerated in animals and can induce HIV-1 antigen-specific

cellular and humoral immune responses. Therefore, we anticipate that these two vaccines will have a good safety profile in humans and are expected to induce favorable immune responses.

#### 4 Scientific Problems to be Solved by this Clinical Trial

This study represents the first clinical trial to evaluate the safety and immunogenicity of a DNA-Tian Tan vaccinia composite AIDS vaccine in humans. The scientific questions it aims to address are outlined in Table 3.

**Table 3. Scientific problems to be solved by this phase Ib clinical trial**

| Problems                                                                                                                                                                                     | Primary safety endpoint events                                                                                                                            |
|-----------------------------------------------------------------------------------------------------------------------------------------------------------------------------------------------------|------------------------------------------------------------------------------------------------------------------------------------------------------------------|
| Is a single intramuscular injection of 2 mg or 4 mg of the DNA vaccine safe?                                                                                                                        | The proportion of participants experiencing grade 3 or higher adverse events within 4 weeks after the first vaccination in each group.                           |
| Is it safe to administer three consecutive intramuscular injections of 2 mg or 4 mg of the DNA vaccine?                                                                                             | The proportion of participants experiencing grade 3 or higher adverse events within 4 weeks after each vaccination in each group.                                |
| Is the combined vaccination regimen of three doses of the DNA vaccine at different doses followed by one dose of the replicating recombinant vaccinia virus vaccine safe?                           | The proportion of participants experiencing grade 3 or higher adverse events from the first vaccination until 24 weeks after the last vaccination in each group. |
|                                                                                                                                                                                                     | Primary immunogenicity endpoint events                                                                                                                    |
| Is there a qualitative or quantitative difference in the immune responses elicited by different doses of the DNA vaccine when boosted with the same dose of the recombinant vaccinia virus vaccine? | Antigen-specific ELISPOT and antibody responses will be measured at weeks 2, 4, 8, and 24 after the last vaccination.                                            |

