### 6.4.2 Immunization and Follow-Up Plan

The Phase Ib clinical trial requires a total of 36 volunteers, including those who have and have not previously received the smallpox vaccine. These volunteers will be divided into three groups: a combined immunization group (24 individuals) receiving three doses of the DNA vaccine and one dose of the rTV vaccine, a DNA-only group (6 individuals) receiving three doses of the DNA vaccine alone, and a placebo group (6 individuals) receiving only a placebo. The combined immunization group is further divided into a low-dose and a high-dose subgroup, each consisting of 12 individuals. Recruitment will aim to include an equal number of individuals who have and have not received the smallpox vaccine in each

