dose subgroup. Enrollment and vaccination will begin with the low-dose subgroup of the combined immunization group in the order of enrollment. The safety of the vaccine will be assessed within two weeks after each DNA vaccination in the low-dose subgroup. If no more than two vaccine-related adverse events of grade  $\geq 3$  (excluding fever above 39°C for no more than 3 days) occur, the trial will continue; if three or more such adverse events occur, subsequent vaccinations will be halted. Participants in both dose subgroups of the combined immunization group and the DNA-only group will receive three doses of 2 mg (low-dose subgroup) or 4 mg (high-dose subgroup) of the DNA vaccine at 4-week intervals. Enrollment and vaccination for the DNA-only group will commence simultaneously with the high-dose subgroup of the combined immunization group. If no more than two vaccine-related adverse events of grade  $\geq 3$  occur after each 4 mg DNA vaccination in the high-dose subgroup and the DNA-only group, the trial will continue; if three or more such adverse events occur, subsequent vaccinations in that dose subgroup will be stopped. If no more than two vaccine-related adverse events of grade  $\geq 3$  occur after the third DNA vaccination in each group, the combined immunization group will receive the rTV vaccine at the dose determined by the Phase Ia trial four weeks after the last DNA vaccination, while the DNA-only group will receive a placebo of the corresponding dose of the rTV vaccine. The placebo group will begin enrollment and vaccination at the same time as the low-dose subgroup of the combined immunization group and will receive placebos of the same volume as the DNA or rTV vaccines at the same time points. After the last vaccine or placebo administration, all participants will undergo at least six consecutive months of clinical and laboratory observation. In the Phase Ib trial, the interval between vaccinations in each group will be  $\geq 4$  weeks; if the time required for adverse reactions to heal or resolve exceeds 4 weeks, the interval between vaccinations will be  $\geq$  the actual time required for healing. The criteria for determining adverse events and their relationship to vaccination are detailed in Appendix 2 and Table 9.

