### **6.10.3 Randomization**

To avoid subjective selection bias by researchers and severe imbalance in sample allocation, a block randomization method will be employed in this trial. The random number table for randomization will be generated by statisticians from the Health Statistics Office of the Chinese Center for Disease Control and Prevention using SAS 9.1.2 software.

The 36 participants will be divided into two phases based on the order of enrollment, with 18 participants in each phase. In the first phase, participants will be randomized in a 2:1 ratio to either the low-dose combined immunization group or the placebo group. In the second phase, participants will be randomized in a 2:1 ratio to either the high-dose combined immunization group or the DNA-only group.

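### Table 3 asks about DNA safety by dose but defines the endpoint by group, so no stated rate covers all 18 people given the same 4 mg DNA

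*Protocol*

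**What the plan says.** Table 3 (protocol section 4) pairs each safety question with a primary safety endpoint. Row 1 asks: "Is a single intramuscular injection of 2 mg or 4 mg of the DNA vaccine safe"? Row 2 asks the same of three consecutive injections. The endpoint for row 1 is "The proportion of participants experiencing grade 3 or higher adverse events within 4 weeks after the first vaccination in each group", and for row 2 "The proportion of participants experiencing grade 3 or higher adverse events within 4 weeks after each vaccination in each group". Primary objective 1 in section 6.1 is also framed by DNA dose.

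The word group has two meanings in the protocol. Section 6.4.2 names three groups: combined (24), DNA-only (6) and placebo (6). It then adds: "The combined immunization group is further divided into a low-dose and a high-dose subgroup, each consisting of 12 individuals". Table 5 lists four arms: DNA-L+rTV (12), DNA-H+rTV (12), DNA (6) and placebo (6).

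On the two arms that receive 4 mg, section 6.10.3 says of the second enrolment phase that "participants will be randomized in a 2:1 ratio to either the high-dose combined immunization group or the DNA-only group". Section 6.4.2 says: "Enrollment and vaccination for the DNA-only group will commence simultaneously with the high-dose subgroup of the combined immunization group". The 4 mg halting rule in the same section covers events "after each 4 mg DNA vaccination in the high-dose subgroup and the DNA-only group", so it names both arms together. Section 6.10.5(3) makes the adverse event analysis descriptive and fixes no columns or denominators.

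**The concern.** The question and the endpoint beside it use different units. Rows 1 and 2 ask about a DNA dose, but the endpoint is a rate per group, and neither meaning of group yields the rate among everyone who received 4 mg DNA. Read as four arms, the evidence at 4 mg appears as two separate small rates. Read as three groups, the combined group's rate averages over two doses, and the only rate purely at 4 mg rests on the six DNA-only participants.

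What is at stake is precision on a primary safety endpoint. The trial has 36 participants and section 6.10.2 gives no precision target, so each participant counts. How firmly an absence of Grade 3 or higher events can be read at the higher dose depends directly on the denominator.

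**Working it through.** **Inputs.** The second phase has 18 participants, allocated 2:1 (section 6.10.3). The arm sizes are 12, 12, 6 and 6 (Table 5). The protocol states no event rate and no interval method. I therefore assume exact (Clopper-Pearson) two-sided 95% intervals and true rates of 5%, 10% and 20%, and I assume that all planned participants receive the dose in question.

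**The plan's own figures.** 18 × 2/3 = 12 and 18 × 1/3 = 6; 12 + 12 + 6 + 6 = 36. The allocation reproduces. The total of 36 is attributed to the regulator's approval requirements, so there is no power or precision calculation to reproduce.

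**Are the 18 one cohort in the relevant window?** In Table 5 both 4 mg arms receive DNA at weeks 2, 6 and 10, and rTV or rTV placebo at week 14. The four-week window after the third DNA dose runs from week 10 to week 14 and so closes when the arms diverge. Both arms come from the same randomisation and start together, and under section 6.10.4 vaccination is blinded until after rTV. Combining them for the DNA doses needs no modelling assumption and does not cross the two enrolment phases.

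**Zero-event upper limit**, 1 − 0.025^(1/n):
- n=6: 1 − 0.025^(1/6) = 45.9%
- n=12: 1 − 0.025^(1/12) = 26.5%
- n=18: 1 − 0.025^(1/18) = 18.5%

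**One event observed**, exact 95% interval: 1/6 gives 0.4% to 64.1%; 1/12 gives 0.2% to 38.5%; 1/18 gives 0.1% to 27.3%.

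**Chance of seeing at least one event**, 1 − (1 − p)^n:

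| Assumed true rate p | n=6 | n=12 | n=18 |
|---|---|---|---|
| 5% | 26.5% | 46.0% | 60.3% |
| 10% | 46.9% | 71.8% | 85.0% |
| 20% | 73.8% | 93.1% | 98.2% |

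**Standard error relative to the pooled 18:** √(18/12) = 1.22 for the 12-person arm and √(18/6) = 1.73 for the 6-person arm.

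**Three-group reading.** The combined group of 24 would give a zero-event limit of 1 − 0.025^(1/24) = 14.2%. That figure describes a mixture of 12 people on 2 mg and 12 on 4 mg, so it bounds the rate at neither dose.

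**The case against.** The other side has a good deal on its side. Reporting by randomised arm is conventional, and 12 and 6 are correct denominators for those arms. The per-arm rates are unbiased, no data are lost, and any reader can add the two numerators to obtain a rate out of 18. Table 3 does not forbid a pooled summary, and a statistical analysis plan, not seen here, could add one. The primary safety endpoints in section 6.2.1.1 do not mention groups at all, so the point rests on the wording of Table 3. The one decision rule for 4 mg DNA already names both arms, so no halting decision changes. The protocol sets no precision target, so none is missed.

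Most of this stands, and it limits the point. A reader might infer that the primary rates are wrong or biased, or that the 4 mg estimate is much less precise throughout. The documents do not support either inference: the rates are valid for their arms, and a large loss applies only to the 6-person arm. For the 12-person arm it is moderate (26.5% against 18.5%). A reader might also conclude that pooled columns should replace the arms. They should not: the pre-boost profile of each arm is needed to interpret row 3, whose period starts at the first vaccination. Row 2, read literally, covers every vaccination including rTV, where the arms must stay separate.

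Deferring to the analysis plan does not remove the mismatch. Table 3 itself labels these as primary safety endpoint events and fixes their unit as the group, next to a question about dose.

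**Conclusion.** The point holds as a mismatch between question and endpoint that costs precision; it is not an error of bias. For the DNA doses in rows 1 and 2, neither reading of group delivers the rate among the 18 people given identical, concurrently randomised 4 mg DNA. Pooling lowers the zero-event upper limit to 18.5%, from 26.5% or 45.9%. At an assumed 10% rate it raises the chance of seeing at least one event to 85%, from 72% or 47%. The 2 mg rate is unaffected under the four-arm reading, because all 12 recipients are in one arm.

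The interval limits rest on exact two-sided 95% intervals and full planned enrolment. The detection chances also rest on assumed event rates, for which the protocol gives no value. The conclusion does not extend to row 3 or to anything from the rTV or rTV-placebo dose onward.

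**What to change.** In Table 3 rows 1 and 2, for the DNA doses only, and in section 6.10.5(3), state that the primary summary of DNA-phase safety, up to the rTV or rTV-placebo visit, is by DNA treatment received: 2 mg (n=12), 4 mg (n=18, both second-phase arms) and DNA placebo (n=6), each with an exact 95% interval. Keep the per-arm display alongside. From the rTV or rTV-placebo dose onward, and for row 3, analyse by the four arms of Table 5, and say in Table 3 that group means those four arms.

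The cost is a change of wording and one additional summary table. No participants, visits, data or clinical procedures change.
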